### Data collection procedures

#### Primary data collection

Primary data collection will consist of telephone interviews, online surveys, and audiotaped treatment sessions from key staff (*i.e*., clinical supervisors and clinicians). Staff from each of the treatment sites that were responsible for A-CRA delivery (or outpatient adolescent treatment in general, if it is reported that A-CRA is no longer being delivered) are being recruited. During the funding period, most programs had two clinicians trained. We used this estimate to budget for data collection and analyses.

All data collection is voluntary and confidential. Our strategy is to use multiple methods (*i.e*., mail, phone, and email) to introduce and remind the participants about the data collection opportunities, consistent with effective tailored survey methods [49]. Prior to the data collection, we explain the purposes of the research through both an email and by phone and then ask for participation in the study. If we are not able to contact by email or phone, the information and request is sent by mail (using FedEx).

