#### Participant recruitment and eligibility criteria

Although the aims and hypotheses of the current study are focused on treatment organizations, it is necessary to collect information from individuals at the funded programs who would be responsible for implementing the treatment. Given our focus primarily on implementation quality, our target population includes clinical supervisors and clinicians responsible for adolescent treatment. In the case that a site no longer has an adolescent SUD treatment program, we attempt to recruit program directors or other administrative staff with knowledge about the organization’s former adolescent SUD treatment program and about how, why, and to what extent A-CRA was or was not sustained after the federal funding ended.

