#### Interviews

Semi-structured phone interviews with clinical supervisors and clinicians at the funded programs are being conducted by trained field interviewers. The interviews are arranged individually with respondents and last approximately 30 to 60 minutes depending on respondent role and experience with A-CRA. Following standard semi-structured interview protocols, the interviews use open-ended (*i.e*., ‘grand tour’) questions followed by focused, standard probes, such as verification and compare-and-contrast questions [50]. We provide respondents with compensation for the interview and surveys ($50).

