#### Intervention characteristics

##### Perceptions of the A-CRA intervention

We assess A-CRA perceptions in a number of ways. In the interviews, we ask an open-ended question about what respondents thought about A-CRA, which will then be coded for analyses. As part of the survey*,* modified items from O’Loughlin *et al*. [26] are used to assess perceived compatibility, difficulty and effectiveness. Following Rogers’ theory of innovation diffusion, we also employ Steckler *et al*.’s [56] relative advantage and complexity scales, shown to have high reliability (alphas = 0.88 and 0.83, respectively).

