##### A-CRA facilitators and barriers

We use items developed by Scheirer *et al*. [17] to ask all supervisors and clinicians about the factors that facilitated and impeded A-CRA delivery regardless of whether they report sustainment or not. If staff report that they are no longer delivering A-CRA, we ask about the reasons for stopping it (*e.g*., ‘When did you stop delivering A-CRA?’, ‘What were the main reason(s) that you stopped delivering it?’) and ask those that report sustainment the reasons that helped them maintain it (*e.g*., ‘What has helped you maintain A-CRA since the loss of CSAT funding?’). We use these data to meet the first study aim.

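### Which staff may answer for a site depends on whether it still delivers A-CRA, so perception and attitude scores can differ by outcome status for reasons of respondent selection

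*Protocol article*

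**What the plan says.** Under Primary data collection, the protocol recruits "Staff from each of the treatment sites that were responsible for A-CRA delivery", with the alternative "or outpatient adolescent treatment in general, if it is reported that A-CRA is no longer being delivered". Under Participant recruitment and eligibility criteria, "our target population includes clinical supervisors and clinicians responsible for adolescent treatment". The only knowledge condition in that section covers sites that no longer have an adolescent program, where "we attempt to recruit program directors or other administrative staff with knowledge about the organization" and its former program. A site that is open but has dropped A-CRA falls under neither an A-CRA training condition nor a knowledge condition.

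Table 2 lists A-CRA perceptions (clinicians) and attitudes (supervisors and clinicians) among the predictors of sustainment. The section on perceptions names survey scales for compatibility, difficulty, effectiveness, relative advantage and complexity. In the interviews, "we ask an open-ended question about what respondents thought about A-CRA". The Analytic plan aggregates all data to program by time and enters the predictors into mixed models for the sustainment outcome. Staff support for A-CRA is the example given for the intervention-characteristics part of the Aim 2 hypothesis.

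For facilitators and barriers, the plan is "to ask all supervisors and clinicians about the factors that facilitated and impeded A-CRA delivery regardless of whether they report sustainment or not". Those data are assigned to Aim 1. The Interviews section recognises that respondents differ in exposure, but only as a determinant of interview length: "depending on respondent role and experience with A-CRA".

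**The concern.** The reported outcome decides who is eligible to supply the predictor. Where A-CRA continues, the scales are answered by people who deliver it. Where it has stopped, they may be answered by people who never did. The Background section expects loss of trained staff to hinder sustainment, so unexposed respondents would tend to gather at non-sustaining sites. Primary data collection says most programs had two trained clinicians, so little turnover is needed before none is left. The oldest cohort is measured about 48 to 72 months after funding ended.

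This differs from ordinary reverse causation, in which one person's opinion changes after the program is dropped. Here the person may change. Aggregation to program level hides that change. A lower or neutral score from staff who do not know A-CRA could then be read as poor perceptions predicting non-sustainment, which is one of the Aim 2 hypotheses. In Aim 1, reasons and barriers at dropped sites may come partly from staff who were not there when A-CRA was delivered.

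**Working it through.** **The plan's own figures.** Estimated sample size and statistical power gives 64 programs, 3 time points and an intra-class correlation of 0.1. It states neither alpha nor power; two-sided 5% and 80% are assumed here, so the multiplier is 1.96 + 0.84 = 2.80.
- Dichotomous predictor: design effect 1 + 2 x 0.1 = 1.2; effective n = 192/1.2 = 160; detectable difference = 2.80 x sqrt(4/160) = 0.443 SD. The plan states about 0.45.
- Continuous predictor: tanh(2.80/sqrt(64 - 3)) = 0.344. The plan states about 0.34.

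Both reproduce. Perception and attitude scores are continuous predictors, so the relevant benchmark is r = 0.34.

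**Induced correlation with no true association.** All of the following are assumptions; the document supplies none of them.
- p = share of sites that dropped A-CRA = 0.5
- q = share of dropped sites answered by unexposed staff = 0.3 to 0.7
- d = difference in score between exposed and unexposed staff = 0 to 0.8 SD
- one score per site, 64 sites, outcome treated as dropped or not

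Formulas:
- gap between outcome groups: g = q x d
- within-group variance: W = 1 + p x q x (1 - q) x d^2
- between-group variance: B = p x (1 - p) x g^2
- r = g x sqrt(p(1 - p)) / sqrt(W + B)
- rejection rate from Fisher's z: Phi(atanh(r) x sqrt(61) - 1.96) + Phi(-atanh(r) x sqrt(61) - 1.96)

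Worst case in the range, q = 0.7 and d = 0.8: g = 0.56; W = 1 + 0.5 x 0.21 x 0.64 = 1.067; B = 0.25 x 0.3136 = 0.078; r = 0.28/sqrt(1.146) = 0.26.

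| q | d | gap (SD) | r | rejection at nominal 5% |
|---|---|---|---|---|
| any | 0 | 0 | 0 | 5% |
| 0.3 | 0.3 | 0.09 | 0.04 | 6% |
| 0.5 | 0.2 | 0.10 | 0.05 | 7% |
| 0.5 | 0.5 | 0.25 | 0.12 | 16% |
| 0.5 | 0.8 | 0.40 | 0.19 | 32% |
| 0.7 | 0.8 | 0.56 | 0.26 | 55% |

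Simulated two-group comparisons (32 against 32 sites) agree closely, with 56% in the last row. Outside this range, if every dropped site were answered by unexposed staff (q = 1, d = 0.8), r would be 0.8 x 0.5/sqrt(1.16) = 0.37.

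**Does any stated analysis remove it?** Site random effects and cohort terms do not remove a bias tied to outcome status. Multiple imputation and nonresponse weights deal with absent answers, not with answers from people who lack the experience asked about. Staff turnover is a listed predictor and may absorb part of the effect, but it is not the respondent's exposure. Using an earlier wave's score cannot help at sites that dropped A-CRA before wave 1.

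**The case against.** A reader might infer that the score shifts automatically when a site drops A-CRA. The protocol does not support that. Former A-CRA staff still at the site remain eligible, and the score moves only if unexposed staff are recruited, complete the scales and answer differently. At d = 0 the induced correlation is zero.

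Nor does the protocol say that A-CRA-naive staff complete the perception scales. The Interviews section hints that content varies with experience, and the questions about stopping go to staff who report that they no longer deliver A-CRA, which presupposes that they once did. Skip rules of this kind often sit in the instruments. This keeps the point conditional. It does not remove it, because the article states the eligibility rule and gives no experience condition with it.

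It is also tempting to set the 0.56 SD gap against the plan's 0.45 SD and call the bias larger than the target effect. Those are unlike quantities: the first is a gap in a predictor between outcome groups, the second a difference in the outcome between two levels of a dichotomous predictor. On the comparable scale the worst case in the range is 0.26, below 0.34. Further, the planned outcome is a graded score and a program's score may average several respondents, so the two-group illustration is only a guide and one unexposed respondent may be diluted.

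Two more limits stand. Facilitator and barrier data are interview material for the mainly qualitative Aim 1, with no score defined (although Table 2 lists the construct among the predictors), so the modelling concern is clearest for perceptions and attitudes. For the 34 AAFT4 sites the primary data include the last quarter of funding, so the difficulty that an earlier wave's score cannot cure lies mainly with older cohorts.

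Finally, general staff are needed at dropped sites for organizational and fidelity data, and scoring perceptions only from exposed staff would leave gaps chiefly at non-sustaining sites. That is a good reason not to make the restricted analysis the only one.

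**Conclusion.** The point holds in conditional form. The protocol makes respondent eligibility depend on the outcome, sets no A-CRA experience condition at open sites that dropped it, and uses the resulting perception and attitude scores to explain that same outcome. Whether bias follows, and how much, cannot be read from the document. With half of 64 sites dropped, 30-70% of those answered by unexposed staff and a shift of 0-0.8 SD, the induced correlation lies between 0 and about 0.26, and false rejection between 5% and about 56%. That range covers a negligible effect and a seriously misleading one, and the stated plan has no means of telling which applies. For Aim 1 the consequence is about the source of the reports: barriers at dropped sites may be partly second-hand. A change is worth making, since it is cheap and only the first of three waves was complete when the article was submitted.

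**What to change.** 1. At every site, whatever its A-CRA status, approach remaining staff with A-CRA training or delivery experience first. Keep recruiting general staff at dropped sites for organizational items and fidelity.
2. Record a respondent-level A-CRA exposure flag (trained, delivered, neither): prospectively in waves 2 and 3, and from the interviews where possible for wave 1.
3. Report the Aim 2 perception and attitude results with and without unexposed respondents.
4. When reporting Aim 1 barriers and reasons for stopping, state whether they come from exposed or unexposed staff.

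The cost is a line in the recruitment script, one extra variable, some recoding of wave 1 interviews and one additional model run. The exposed-only analysis loses some non-sustaining sites. It is therefore less precise, and its missingness is related to the outcome, so it should be shown beside the all-respondent result and not replace it.

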#### Interviews

Semi-structured phone interviews with clinical supervisors and clinicians at the funded programs are being conducted by trained field interviewers. The interviews are arranged individually with respondents and last approximately 30 to 60 minutes depending on respondent role and experience with A-CRA. Following standard semi-structured interview protocols, the interviews use open-ended (*i.e*., ‘grand tour’) questions followed by focused, standard probes, such as verification and compare-and-contrast questions [50]. We provide respondents with compensation for the interview and surveys ($50).

#### Surveys

After the semi-structured telephone interview, we ask respondents to complete an online survey to ascertain characteristics of the facility in which the treatment was delivered that will serve as covariates in our analyses (*i.e*., program-specific factors) and other standardized scale measures of organizational or clinical support (see Table 2 for a list of measures). Our experience with data collection suggests that higher survey response rates will be achieved if it is conducted following the interviews, and this is also consistent with recent data collection approaches in this field [51].

**Table 2 Tab2:** **Predictors of sustainment, measures, and data collection methods**

***Construct***	***Dimension***	***Measurement source***	***Data collection methods***	***Respondent(s)***
**Community/environment factors**				
External support	▪ Funding for intervention-related services	Knudsen 2009 [53]	Interview & Survey	Supervisor
Community participation	▪ Intervention-relevant referrals	Knudsen 2009 [53]	Survey & Interview	Supervisor
	▪ Dissemination efforts and community involvement	Scheirer *et al*. 2008 [17]		
**Implementation during the funding period-related factors**				
Quantity and quality	▪ # of clients served, # of clinicians certified, # of supervisors certified, average # of sessions provided per participant	Archival data	NA	NA
Client outcomes	▪ 12-month recovery status	Archival data	NA	NA
**Organizational factors**				
Organizational type and capacities	▪ Agency type, services offered, payment sources, age of program, client size and composition	N-SSATS [44]; Knudsen 2009 [53]	Interview & Survey	Supervisor
				Supervisor
	▪ Staff levels & qualifications	Knudsen 2009 [53]	Survey	Supervisor
	▪ Staff turnover (*annual rates, key personnel*)		Survey	
	▪ Sustainability capacity	Wash U, 2012 [55]	Survey	Supervisor
Leadership support	▪ Managerial support for EBT	O’Loughlin *et al*. 1998 [26]; Aarons *et al*., 2013 [54];	Survey & Interview	Clinician
	▪ EBT champion(s)			Clinician
		O’Loughlin *et al*. 1998 [26]		
Organizational Readiness to Change	▪ Motivation to change, resources, staff attributes, organizational climate	Lehman *et al*. 2002 [35]	Survey	Clinician
**Intervention characteristics**				
EBT perceptions	▪ Perceptions of the EBT intervention (a)	(a) Steckler *et al*. 1992 [56]; O’Loughlin *et al*. 1998 [26]	(a) Interview & Survey	Clinician (a)
	▪ Attitudes toward the EBT intervention (b)			Supervisor & Clinician (b, c, d)
	▪ Plans for EBT sustainment or spread (c)	(b) Lin *et al*. 2005 [57]; O’Loughlin *et al*. 1998 [26]	(b) Interview & Survey	
	▪ Perceived implementation facilitators and challenges (d)	(c & d) Scheirer *et al*. 2008 [17]	(c & d) Interview	

#### Treatment sessions

Following the interview, participants that report providing direct services to youth are asked to submit recorded therapy sessions so that treatment fidelity can be assessed. A technology-assisted system similar to one used during the funding period is being used. This system allows clinicians to upload digitally recorded audiotaped clinical therapy sessions, and its secure role-based system limits access to only one’s own recordings. Clinicians are provided with instructions to obtain client consent to record the treatment sessions. Respondents who are asked to provide recorded therapy sessions receive an additional $50 incentive for this data collection component.

### Study measures

#### Sustainment

We are studying the extent to which A-CRA is sustained by assessing implementation quality. Consistent with Fixsen *et al*.’s [11] and Scheirer and Dearing’s [16] definition of implementation, we operationalized implementation quality by evaluating the functional components of the treatment, including the organizational supports of training and monitoring (*i.e*., supervision), along with treatment quality (treatment fidelity).

The organizational supports for A-CRA delivery includes eight elements: a) clinical knowledge in A-CRA, b) execution of a planned number of treatment sessions at or above the minimum required by developer, c) presence of a certified clinician(s) delivering A-CRA, d) presence of a certified A-CRA supervisor, e) bi-weekly supervision that is aligned with the developer manual, f) supervision that includes review of recorded sessions, g) a training process that meets quality requirements required during implementation, and h) a clinical certification process that mirrors one used during implementation. These elements are based on those that were used during the federal funding period to monitor implementation. Treatment fidelity is assessed via recorded therapy sessions. Clinicians that are currently delivering adolescent SUD treatment services will be identified and asked to upload a sample for assessment. Fidelity ratings will be completed by an expert rater under the supervision of the treatment developer from Chestnut Health Systems, using the A-CRA rating manual [48]. The manual provides operational definitions of each rating option (on a 5-point scale) for each A-CRA procedure. We will compute an average treatment fidelity rating for each clinician based on the ratings across the submitted session. We will then average the fidelity ratings across clinicians at an organization to obtain a program-level treatment fidelity rating. If we learn that one clinician at a site delivers treatment to substantially more clients than another clinician, then we will consider weighting the fidelity data to adequately represent this difference in treatment delivery among clinicians at a program. For this measure, we will create an additive measure by summing up scores on each of the implementation quality components to derive a site-level sustainment score.

#### Predictor measures

We selected measures that have demonstrated good reliability and validity in previous studies. However, given that this area of study is relatively new, we also had to adapt existing measures for the purposes of the current study, and develop measures when necessary. The psychometric properties of all measures, including new or adapted ones, will be examined within our sample using exploratory and confirmatory factor analysis. Our predictors of sustainment measures are shown in Table 2.

#### Community environment factors

Supervisors are asked about local, state and federal support (external support) since the end of federal funding. In these contexts, community participation typically encompasses the provision of referrals to receive care. We ask supervisors about the main sources of A-CRA referral and of their treatment program overall. We ask this in both the interview and survey to capture: a) descriptive information about the reasons for the different referral sources and document any changes over time to help address community need, and b) systematically collect comparable information across the programs on their main sources of referral. We also ask questions related to dissemination efforts and community involvement in the treatment to capture efforts made by the organization to build community support for their program [17]. Supervisors will be asked about the introduction and continuation of other adolescent SUD treatment providers in their area to assess community need changes.

#### Implementation-related factors

A number of variables will be used to characterize implementation during the federal funding period. These include: the number of adolescents treated, the average number of treatment sessions each client received, the average treatment length of stay, and the number of supervisors and clinicians achieving supervisor and clinician certification. We will also use client outcome data collected during the period. Specifically, data were collected using the Global Appraisal of Individual Needs (GAIN; [52]). These data will be used to examine the proportion of clients in recovery 12 months after treatment intake. Data from over 6,000 adolescents receiving A-CRA is available. We anticipate that clients will have the following characteristics based on the current data available: 72.8% male, 31.7% Caucasian, 30.0% Hispanic, 17.5% African American, 20.8% Other. Average age is 16.2 years, 84.4% are attending school, and 51.0% are from a single parent household. Clinically, 90.3% have used alcohol in their lifetime (76.4% to intoxication) with a median age of first use of 13.0 and a median of 3.0 years of use. During the 90 days prior to intake, 57.8% had consumed alcohol (40.7% to intoxication). The latter includes 76.4% consuming a peak of more than five standard drinks. Over 86% of alcohol use was in combination with marijuana or another drug.

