The level of implementation refers to how well an EBT was delivered during the funding period. In this study, we assess level of implementation in reference to employing clinical and supervisory staff who have demonstrated competency through the certification processes and an organization having recruited and treated a sufficient number of participants during the initial implementation period, also termed as ‘penetration’ [32,33]. Integral to Rogers’ [20] innovation diffusion theory is that the implementation experience will have a large influence on sustainment. Poor implementation may lead to ‘discontinuance’ (*i.e*., rejection) of an innovation. We have available participant process (*e.g*., treatment initiation, engagement, satisfaction) and outcome data to help explicate implementation during the funding period. Opinions are mixed as to whether these data will help predict level of sustainment [34]. Intuitively, it is sensible to expect that the extent to which clinicians are able to engage participants in an intervention or participants are able to achieve a treatment’s objectives would be related to sustainment. However, such factors as external (*i.e*., community) or internal (*i.e*., organizational) support may trump any efforts to sustain an effective EBT. Therefore, we examine these issues in our study.

Factors within the organizational setting refers to characteristics of the ‘inner context’ [29], such as institutional (*e.g*., leadership support, resources within the organization for EBT delivery), organizational climate [35], and staff attributes (*e.g*., presence of a program champion, motivation and skills to deliver the EBT). Although studies have shown that staff turnover is not predictive of sustainment [17], we believe that with a complex treatment like A-CRA, attrition of trained staff will impede sustainment. Intervention characteristics, such as community-based providers’ perceptions of the treatment, may influence whether it is sustained [20]. It is not known whether program leadership will still be in support of the treatment at the end of the grant period and whether staff will be motivated and trained to deliver it, so we plan to assess these factors in this study.

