#### Secondary data

Extensive data was collected during the funding period on implementation quality and organizational functioning. Records of the number of clinicians and supervisors trained and certified at each funded program, and the number of sessions and A-CRA procedures delivered to each client were recorded. Data from clinical staff on organizational functioning was also collected. In addition, the number of adolescents that were treated at each funded program, the number of treatment sessions each client received, and the treatment length of stay was recorded. The client-level outcome dataset that contains baseline, 3-, 6-, and 12-month follow-up data on substance use and functioning is available from clients who receive A-CRA at the funded sites. No individual-level identifiers are included in the secondary dataset. This dataset will be useful to help characterize implementation quality during the funding period and serve as predictor variables to test our hypothesis as to whether programs that were able to successfully implement A-CRA during the funding period are more likely to sustain it than programs that were not successful at implementation during the funding period.

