### Analytic plan

This study involves the use of both qualitative and quantitative analytic methods. The first aim of describing sustainment and the associated innovations, facilitators and barriers will be addressed primarily with qualitative methods. We employ multiple strategies to avoid bias in the analysis and interpretation of the qualitative data by including the use of a multidisciplinary team (rather than a single observer) to collect and analyze the data. In addition, standardized instruments along with semi-structured interview protocols are used to decrease the possibility of bias.

Raw data will be cleaned and descriptive statistics will be conducted at first to check the data quality and integrity for every variable in the raw data. In case of missing information on the quantitative measures, multiple imputation and nonresponse weights will be implemented [59]. All data will be aggregated to the program by time level for subsequent analyses. We recognize that our study design includes data from different time points based on when the organization lost or will lose funding and our proposed data collection period (2013 to 2015). The mixed model can handle these unsynchronized longitudinal measurements so that we can consistently estimate the association between the predictors and the proposed outcomes.

Next, preliminary exploratory analyses will estimate the unadjusted mean trajectories of sustainment outcomes over time among all sites as well as for each site by growth curve models [60] to address the goals of the first study aim. A cluster analysis will [61] identify potential groups of sites where sites in a group will have relatively similar trajectories. If such groups exist, descriptive statistics will be conducted to summarize and compare the mean characteristics of all groups.

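### The client-outcome predictor is a 12-month recovery proportion with no reference to intake status, although baseline client data are held; its association with sustainment may be confounded or attenuated

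*Protocol article*

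**What the plan says.** The Implementation-related factors section lists the variables that describe implementation while federal funding lasted: "the number of adolescents treated, the average number of treatment sessions each client received, the average treatment length of stay", plus certification counts. It then adds client outcomes measured with the GAIN: "These data will be used to examine the proportion of clients in recovery 12 months after treatment intake". Table 2 repeats the measure, with archival data as the source, as "12-month recovery status".

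The purpose is stated in two places. The Background finds it sensible to expect that the extent to which "participants are able to achieve a treatment’s objectives would be related to sustainment", while noting that opinion on this is divided. The Secondary data section says the archival data will help test whether "programs that were able to successfully implement A-CRA during the funding period are more likely to sustain it".

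The same section describes what is held at client level: "baseline, 3-, 6-, and 12-month follow-up data on substance use and functioning". The Analytic plan adds: "All data will be aggregated to the program by time level for subsequent analyses". The Aim 2 mixed model controls for funding cohort. Table 2 also lists client composition among the organizational factors, reported by supervisors during the study's own data collection.

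**The concern.** A status at 12 months, taken alone, does not separate what a program achieved from the condition in which its clients arrived. Two programs that deliver A-CRA equally well can show different recovery proportions if one admits youth with lighter use or fewer problems.

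Two consequences follow for the client-outcome coefficient in Aim 2:

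- **Attenuation.** Case-mix variation unrelated to sustainment acts as noise in the predictor and pulls the association toward zero.
- **Confounding.** Case mix may be tied to grant type, referral source and outer-context funding, which the article treats as possible drivers of sustainment. The coefficient can then pick up that link, in either direction, and be read as evidence about implementation success.

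The planned controls do not close this gap. Cohort adjusts for funding wave. Supervisor-reported client composition is collected from 2013 to 2015, at the earliest in a program's last funding quarter, and the only client content the article names for it is age range. Neither measures the intake severity of the clients who produced the recovery rate. Once data are aggregated to program level, client-level adjustment is no longer possible, so it has to be planned before that step.

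**Working it through.** **1. The plan's own benchmark.** The sample-size section gives a detectable correlation of about 0.34 for a continuous predictor with 64 programs. Assuming a two-sided 5% level and 80% power (neither is stated), Fisher's z gives r = tanh((1.960 + 0.842)/√(64 − 3)) = tanh(0.359) = 0.344. The figure reproduces. It is not disputed and serves below as a reference value.

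**2. Can case mix plausibly differ?** From Table 1:

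- Juvenile drug court: 3 + 1 = 4
- Juvenile drug treatment court: 6 + 1 + 2 = 9
- Offender re-entry: 6 + 1 = 7

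The total is 20 of 84. The other 64 are 2 Targeted Capacity Expansion grantees and 62 with none of these grants. This shows different routes into treatment. It does not measure severity.

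**3. Sampling noise in one program's rate.** The article cites over 6,000 clients and 84 programs: 6,000/84 = 71.4 per program on average. The standard error is √(0.30 × 0.70/71.4) = 5.4 points at a 30% rate and √(0.50 × 0.50/71.4) = 5.9 points at 50%. The rates are assumptions; the article gives none.

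**4. How much could case mix matter?** Write the variance of the unadjusted program rate as program effect + case mix + sampling. Assume a between-program SD of 5 to 10 points for true program effect and 2 to 10 points for case mix. If case mix is unrelated to sustainment, the observed correlation is the true one times the square root of the program share. Full adjustment removes the case-mix term. Variances are in squared percentage points.

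| Rate | Program SD | Case-mix SD | Total variance | Case-mix share | Program share, raw | Program share, adjusted | Observed r if true r = 0.34: raw / adjusted |
|---|---|---|---|---|---|---|---|
| 30% | 10 | 2 | 100 + 4 + 29.4 = 133.4 | 3% | 75% | 77% | 0.29 / 0.30 |
| 30% | 5 | 5 | 25 + 25 + 29.4 = 79.4 | 31% | 31% | 46% | 0.19 / 0.23 |
| 50% | 10 | 10 | 100 + 100 + 35 = 235 | 43% | 43% | 74% | 0.22 / 0.29 |
| 30% | 5 | 10 | 25 + 100 + 29.4 = 154.4 | 65% | 16% | 46% | 0.14 / 0.23 |
| 50% | 5 | 10 | 25 + 100 + 35 = 160 | 62.5% | 16% | 42% | 0.13 / 0.22 |

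Over the whole assumed range, case mix is 3% to 65% of the variance. A true correlation of 0.34 appears as 0.13 to 0.29 unadjusted and 0.22 to 0.30 adjusted.

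**5. Confounding.** Suppose true program performance has no relation to sustainment, but case mix correlates with it at 0.34 (an assumed value, borrowed from step 1 for scale). The apparent correlation of the raw rate is then 0.34 × √0.03 = 0.06 up to 0.34 × √0.65 = 0.27, and its sign follows that of the case-mix relation.

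**The case against.** **Silence on adjustment.** The article never calls the proportion unadjusted, and a fuller protocol or analysis plan might define it differently. This stands in part. But two places in the article name an end-state measure, and neither points to a change score or an expected rate.

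**The observed rate may be the intended construct.** Staff may decide to continue A-CRA because of the outcomes they see, whatever the case mix. This stands, and is why the raw proportion should be kept as a sensitivity analysis. It does not serve the other stated use, as evidence of successful implementation.

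**Partial controls exist.** Agency type, client composition and cohort may absorb some case mix. So might program type, which the sample-size section names as an example predictor. They are not intake severity.

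A reader might also infer more than the documents support:

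- *That program success rests on this measure.* It is one of several implementation predictors. The outcome is the site-level sustainment score.
- *That the rate mainly reflects admissions or natural course.* No variance, recovery rate or untreated course is given, and the assumed range runs from trivial to dominant.
- *That many clients count as recovered without change.* The article implies 100 − 57.8 = 42.2% with no alcohol use in the 90 days before intake. That figure is pooled over programs and covers alcohol only; it does not show abstinence from other drugs.
- *That programs are known to admit very different youth.* Table 1 counts grants, not severity.
- *That case mix exceeds sampling noise.* Suppose recovery is 60% in non-users and 35% in users at intake. Programs with 25% and 60% non-users then differ by 0.25 × 35 = 8.75 points. The fair comparison is with the SD of a difference between two programs, √2 × 5.9 = 8.3 points, not with the 5.9 of a single program.

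**Conclusion.** The point holds as a limited one. The client-outcome predictor is specified as a 12-month end state without reference to intake. It is put forward as a sign of implementation success, and the baseline data needed to improve it are already held. Its association with sustainment may be confounded or attenuated.

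The size cannot be determined from the article. The ranges in the working rest on assumed recovery rates and SDs, on equal program sizes of about 71, and on case-mix adjustment that is complete; adjustment on measured variables would recover less. At the low end the change would hardly be noticed. At the high end an association of the size the study is planned to detect would be reduced to 0.13 unadjusted, against 0.22 adjusted.

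No figure in the article changes. The sustainment score and the definitions of the other predictors are unaffected. This is a cheap improvement to one named predictor, not an error that undermines Aim 2.

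**What to change.** - Before aggregating to program level, fit a client-level model (for example, mixed logistic) of 12-month recovery on intake GAIN substance use and severity and basic demographics.
- Carry one value per program into the Aim 2 model: observed versus expected recovery, or the shrunken program effect. Shrinkage also steadies programs with few clients. A single adjusted value avoids adding many case-mix covariates to a model with about 64 programs.
- Repeat the Aim 2 model with the raw proportion as a sensitivity analysis, since programs may respond to the outcomes they observe.
- State in the plan which version is the main one before the association is examined.

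The cost is one extra model on data already held, with no new collection. The downside is a predictor that is slightly harder to explain than a plain proportion.
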